#### Rate of IRIS until 10 weeks

We will model the rate of IRIS over time with a cause-specific hazards model, taking into account the competing risk of prior death. CM-related IRIS will be defined as per the recent proposed definition (see Appendix 2) [40].

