### Overview of the trial

A multicentre double-blind randomised placebo-controlled trial of adjunctive treatment with dexamethasone in adults with HIV-associated cryptococcal meningitis

**Study aim:** To reduce mortality from cryptococcal meningitis in HIV-infected adult patients

**Intervention:** Dexamethasone in a reducing dose over the first 6 weeks of treatment

**Randomisation:** 1:1 study-intervention versus placebo, by using variably sized blocks and stratified by site

**Primary end point:** Survival during the first 10 weeks after randomisation

**Antifungal therapy:** Amphotericin B, 1 mg/kg/day + fluconazole 800 mg/day for 2 weeks, followed by fluconazole, 800 mg/day for 8 weeks, followed by secondary prophylaxis with fluconazole, 200 mg/day

**Secondary end points:** Survival during 6 months after randomisation, disability, rates of fungal clearance, rates of visual impairment, rates of IRIS, rates of new AIDS-defining illnesses, frequency of grade 3, grade 4, or serious adverse events, rates of increased intracranial pressure, time to new neurologic events, health economics analysis.

**Sample size:** 880 patients (roughly equal numbers from Asia and Africa)

**Participating countries:** Uganda, Malawi, Vietnam, Thailand, Indonesia, Laos

**Study sponsor:** Oxford University

**Study funding:** The UK Department for International Development, The Wellcome Trust (UK), and the Medical Research Council (UK) Joint Global Health Trials Scheme

**Study duration (recruitment and follow-up):** 3 years (Figures 1 and 2).

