#### Antiretroviral therapy

All patients must to be referred to local HIV services as soon as practicable, preferably while still admitted to hospital, to ensure that they have access to locally available HIV services, including counselling and ARVs.

It is not clear when antiretroviral therapy should be started in CM. Large studies are currently under way to answer this question. Early initiation may offer faster immune reconstitution benefiting survival, or may increase the risk of IRIS and drug toxicities, adversely affecting survival. In the absence of reliable data, most physicians would recommend starting ARVs after 4 weeks of antifungal treatment, provided the patient has made a good response. The date that ARVs are started (or stopped) in patients in the study will be recorded.

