**Other**		
Indeterminate cerebral lesion (s)	Neurologic illness, with evidence for an intracerebral lesion by brain scan, where the differential diagnosis is either cerebral toxoplasmosis. PML, cerebral lymphoma, or HIV encephalopathy	

Based on 1993 Revised CDC classification system (MMWR 1992; 41(RR-17): 1-19) and modified for this trial.

Visual deficit (at week 10)IRISIncreased intracranial pressure (clinical or measured)

Uniform management of patients and recording of data will be ensured by the local study staff, who will do clinical assessments daily while admitted and at follow-up visits.

Disability and mortality at 6 months and evidence of morbidity (including IRIS) since last seen (week 10) will be collected with either a structured telephone interview or an outpatient visit. Outpatient visits may occur in the patient’s home when the patient cannot come to the hospital.

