##### Adverse events

The frequency of serious and grade 3 and 4 adverse reactions as well as the frequency of specific adverse events will be summarised (both in terms of the total number of events as well as the number of patients with at least one event). The proportion of patients with at least one such event (overall and for each specific event separately) will be summarised and (informally) compared between the two treatment groups based on the Fisher Exact test.

**The rate of IRIS and the rate of relapse** (defined as antifungal treatment intensification or re-treatment) will be modelled with cause-specific proportional hazards models stratified by continent, taking into account the competing risk of prior death. Cumulative incidence functions for the competing events will also be calculated and displayed by treatment arm. Secondary time-to-event end points (time to new AIDS-defining illness or death and time to new neurologic event or death) will be analysed with Kaplan-Meier curves and Cox regression models, as described for the primary end point expressed earlier. The proportion of patients with blindness or visual deficit will be compared between the two arms with a logistic regression (as for the proportion of patients with good disability described earlier).

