### Clinical criteria

Event occurs within 12 months of ARV initiation, reintroduction, or regimen switching after previous failureClinical disease worsening with one of the following inflammatory manifestations of cryptococcosis:MeningitisLymphadenopathyIntracranial space-occupying lesion or lesionsMultifocal diseaseCutaneous or soft-tissue lesionsPneumonitis or pulmonary nodules

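### The only stated IRIS analysis ends at week 10, four weeks after study drug stops, so it does not separate postponed from prevented IRIS; the 6-month IRIS data already collected should support a second analysis

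*Protocol article*

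**What the plan says.** All references are to the protocol article.

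- **Aim and end point.** Secondary aims names the effect on IRIS incidence without a time limit. Secondary end points fixes the limit in its title, "Rate of IRIS until 10 weeks", and specifies a cause-specific hazards model with prior death as competing risk.
- **Analysis.** Analysis of secondary end points treats "The rate of IRIS and the rate of relapse" together: proportional hazards stratified by continent, with cumulative incidence by arm. It gives no later horizon for IRIS.
- **Study drug.** Overview of the trial: "Dexamethasone in a reducing dose over the first 6 weeks of treatment". Table 4 shows it stopping from week 7.
- **ARV timing.** Antiretroviral therapy leaves the start open but notes that "most physicians would recommend starting ARVs after 4 weeks of antifungal treatment", provided the response is good. It adds: "The date that ARVs are started (or stopped) in patients in the study will be recorded".
- **Case definition.** Appendix 2 requires the patient to be on ARVs and sets the time limit as "Event occurs within 12 months of ARV initiation", or within the same period of reintroduction or a regimen switch.
- **Late data.** Clinical monitoring, on the 6-month telephone interview or visit: "evidence of morbidity (including IRIS) since last seen (week 10) will be collected".
- **Other horizons.** Survival, disability and relapse are taken to 6 months. The stated reason for 6-month survival is to check that a 10-week benefit lasts.

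**The concern.** Rationale for adjuvant treatment with dexamethasone cites IRIS as a condition in which guidelines think steroids may help, so a reader will look to this end point for evidence of benefit. An anti-inflammatory drug that is given for 6 weeks and then withdrawn may prevent IRIS or only defer it. If it defers, some cases move from before week 10 to after it and drop out of the stated analysis. The dexamethasone arm then shows a lower IRIS rate although the eventual number of cases is the same.

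At stake is the meaning of a favourable 10-week IRIS result: fewer cases, or the same cases later. The window also leaves out much of the time at risk, which lowers the event count. The protocol guards against a short-lived gain for survival by looking again at 6 months, but states no such check for IRIS.

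**Working it through.** The protocol gives no event rate or power for IRIS, so there is no stated figure to reproduce. The check is calendar arithmetic followed by an illustration.

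**1. Calendar arithmetic.** Inputs: drug ends at week 6 (Overview, Table 4); end point closes at week 10; usual ARV start at week 4 (Antiretroviral therapy); 6 months taken as 26 weeks; 12 months as 52.

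- From end of drug to end of window: 10 − 6 = 4 weeks.
- From usual ARV start to end of window: 10 − 4 = 6 weeks, of which 6 − 4 = 2 are still on study drug.
- Share of the 12-month case-definition window: 6/52 = 12% at week 10, against (26 − 4)/52 = 22/52 = 42% at 6 months.

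For ARV start in week s, at-risk time is 10 − s to week 10 and 26 − s to week 26:

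| ARV start (week) | To week 10 | To week 26 | Share |
|---|---|---|---|
| 4 | 6 | 22 | 27% |
| 5 | 5 | 21 | 24% |
| 6 | 4 | 20 | 20% |
| 8 | 2 | 18 | 11% |

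**2. Illustration of pure postponement.** These are assumptions, not figures from the protocol: all patients start ARVs at week 4; onset among susceptible patients is exponential with median m weeks; dexamethasone suppresses IRIS fully until it stops at week 6 and prevents none; deaths and patients on ARVs at entry are left out.

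F(t) = 1 − exp(−ln 2 × t/m) = 1 − 2^(−t/m). Time at risk to week T is T − 4 on placebo and T − 6 on dexamethasone, so the risk ratio is F(T − 6)/F(T − 4).

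| m | F(4) | F(6) | Ratio, week 10 | F(20) | F(22) | Ratio, week 26 | Placebo events by week 26 seen by week 10, F(6)/F(22) |
|---|---|---|---|---|---|---|---|
| 4 | 0.500 | 0.646 | 0.77 | 0.969 | 0.978 | 0.99 | 66% |
| 8 | 0.293 | 0.405 | 0.72 | 0.823 | 0.851 | 0.97 | 48% |
| 12 | 0.206 | 0.293 | 0.70 | 0.685 | 0.719 | 0.95 | 41% |

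**3. Sensitivity to the suppression assumption.** Weeks 5 and 6 are the lowest doses in Table 4, so full suppression may be too much to assume. If the hazard were only halved in those two weeks, the dexamethasone arm would lose 1 effective week instead of 2:

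- Week 10, F(5)/F(6): 0.580/0.646 = 0.90, 0.352/0.405 = 0.87 and 0.251/0.293 = 0.86 for m = 4, 8 and 12.
- Week 26, F(21)/F(22): 0.974/0.978 = 1.00, 0.838/0.851 = 0.98 and 0.703/0.719 = 0.98.

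If the effect instead outlasted the drug, giving a 4-week delay, the week-10 ratio F(2)/F(6) would be 0.45, 0.39 and 0.37, against 0.98, 0.93 and 0.90 at week 26 from F(18)/F(22).

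In every case the 26-week ratio lies closer to 1 than the 10-week ratio. The size at week 10 depends almost wholly on assumptions.

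**The case against.** Week 10 has a practical basis. It is the last scheduled clinic visit, whereas the 6-month contact may be a telephone call. Appendix 2 requires an initial response, worsening with an inflammatory feature, and exclusion of inadequate antifungal treatment, other infection or malignancy and, if possible, ARV failure. A call alone may not establish this or date it well. The comparison with the 6-month end points is therefore not like for like: death and disability can be learned by telephone, and relapse was given a deliberately pragmatic definition because late episodes may be treated elsewhere. The closer relatives of IRIS, namely AIDS-defining illness and neurologic events, also stop at week 10. This stands, and it argues against replacing the week-10 end point.

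A reader might infer that the trial cannot tell prevention from delay. The documents do not support that. IRIS to 6 months and ARV dates are collected, and the planned cumulative incidence curves could show a rise in weeks 6 to 10. The gap is in the stated analysis, not in the data.

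The illustration is also one-sided. Less than full suppression shrinks it, and it omits patients on ARVs at entry, a predefined subgroup of unstated size who may be at risk sooner. Since Appendix 2 requires cryptococcal disease diagnosed before ARVs, some of them may qualify only after reintroduction or a switch.

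An unseen analysis plan might add a later summary. However, this document fixes the horizon in the end point itself.

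**Conclusion.** The point holds as a gap in one secondary end point. The only stated IRIS analysis closes 4 weeks after study drug ends and about 6 weeks after the usual ARV start, and the later IRIS data have no stated use. A lower 10-week rate could be postponement, and that analysis would not distinguish it from prevention.

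The timing facts come from the protocol; the ARV start is described practice, not a rule. The size of any distortion is unknown. The ratios of 0.70 to 0.77 at week 10 against 0.95 to 0.99 at week 26 show what pure postponement would look like under the listed assumptions. They do not predict this trial's result, and it would be wrong to infer that a 10-week reduction must be an artefact. Nothing in the protocol is contradictory here, and the primary mortality analysis is untouched. The change is worth making because it lets the trial check, from data it already gathers, whether an early IRIS difference persists after withdrawal.

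**What to change.** - Keep the week-10 end point as the clinic-assessed result and describe it as early IRIS.
- Add a prespecified supporting analysis of IRIS to 6 months from the data already collected: cumulative incidence by arm, and a cause-specific hazard model stratified by continent with death as competing event.
- Classify events after week 10 as meeting Appendix 2 or as reported/probable. Treat their dates as approximate, or as interval-censored where needed.
- If a hazard ratio after week 6 is shown, label it descriptive: it conditions on being alive and IRIS-free at week 6 and is not a clean randomised comparison.

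**Cost.** Protocol and analysis-plan wording, plus a classification rule for late events; no new visit or test. The downside is that events after week 10 are partly reported by telephone and so less well dated and classified, in both blinded arms. That is why the 6-month analysis should support the week-10 one and not replace it. Trial status reports 417 of 880 patients recruited by 6 August 2014, so the change could be made during recruitment while the study statistician is still blinded.

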#### Time to new AIDS-defining illnesses or death until 10 weeks

AIDS-defining illnesses will be defined as per the WHO classification (see Table 2).

**Table 2 Tab2:** **WHO clinical staging for HIV/AIDS**

**Clinical stage 1**	Asymptomatic
	Persistent generalised lymphadenopathy (PGL)
	Performance scale 1: asymptomatic, normal activity
**Clinical stage 2**	Weight loss, <10% of body weight
	Minor mucocutaneous manifestations (seborrheic dermatitis, prurigo, fungal nail infections, recurrent oral ulcerations, angular cheilitis)
	Herpes zoster, within the last 5 years
	Recurrent upper respiratory tract infections (for example, bacterial sinusitis)
	And/or performance Scale 2: symptomatic, normal activity.
**Clinical stage 3**	Weight loss, >10% of body weight
	Unexplained chronic diarrhoea, >1 month
	Unexplained prolonged fever (intermittent or constant), >1 month
	Oral candidiasis (thrush)
	Oral hairy leukoplakia
	Pulmonary tuberculosis, within the past year.
	Severe bacterial infections (for example, pneumonia, pyomyositis)
	And/or Performance scale 3: bedridden, <50% of the day during the last month
**Clinical stage 4**	HIV wasting syndrome, as defined by CDC^1^
	*Pneumocystis carinii* pneumonia
	Toxoplasmosis of the brain
	Cryptosporidiosis with diarrhoea, >1 month
	Cryptococcosis, extrapulmonary
	Cytomegalovirus (CMV) disease of an organ other than liver, spleen, or lymph nodes
	Herpes simplex virus (HSV) infection, mucocutaneous >1 month, or visceral of any duration
	Progressive multifocal leukoencephalopathy (PML)
	Any disseminated endemic mycosis (for example, histoplasmosis, coccidioidomycosis)
	Candidiasis of the oesophagus, trachea, bronchi, or lungs
	Atypical mycobacteriosis, disseminated
	Nontyphoid *Salmonella* septicaemia
	Extrapulmonary tuberculosis
	Lymphoma
	Kaposi sarcoma (KS)
	HIV encephalopathy, as defined by CDC^2^
	And/or Performance scale 4: bedridden, >50% of the day during the last month

(Note: Both definitive and presumptive diagnoses are acceptable).

^1^HIV wasting syndrome: weight loss of >10% of body weight, plus either unexplained chronic diarrhoea (>1 month), or chronic weakness and unexplained prolonged fever (>1 month).

^2^HIV encephalopathy: clinical finding of disabling cognitive and/or motor dysfunction interfering with activities of daily living, progressing over weeks to months, in the absence of a concurrent illness or condition other than HIV infection that could explain the findings.

#### Visual deficit at 10 weeks

Retrospective data from HIV-uninfected patients with meningitis due to *Cryptococcus gattii* suggest that steroids may have a profound effect in reducing visual loss; 10% of Vietnamese HIV patients have visual impairment at 10 weeks [41]. We will compare the incidence of blindness and other visual deficits between treatment groups. Visual deficit will be assessed by using a simple 6-point scale (see Table 3).

**Table 3 Tab3:** **Visual assessment**

Visual assessment – record the best performance	
**Function**	**Score**
Normal	1
Blurred	2
Finger counting	3
Movement perception	4
Light perception	5
No light perception	6

#### Time to new neurologic event or death until 10 weeks

A neurologic event is defined as a decrease in Glasgow coma scale score by ≥2 points for ≥2 days from the highest previously recorded Glasgow coma scale score (including baseline) or the occurrence of any of the following adverse events: cerebellar symptoms, coma, hemiplegia, paraplegia, seizures, cerebral herniation, new-onset blindness or deafness, or cranial nerve palsy.

#### Longitudinal measurements of intracranial pressure during the first 2 weeks

Intracranial pressure (ICP) will be measured at study entry, days 3, 7, and 14, and if clinically indicated (depending on local practice). The main outcomes are longitudinal ICP measurements until day 14, and we will model the effect of dexamethasone on ICP based on a joint model for longitudinal and survival data similar to the model described for rate of CSF sterilization, above.

Clinical need and local practice will determine the frequency of lumbar punctures after day 14 and clinician’s diagnoses of increased ICP based on the presence of headache, nausea, diurnal and postural variation, relief with lumbar puncture, and presence of papilloedema will be somewhat subjective.

#### Antifungal treatment intensification or retreatment for cryptococcal meningitis in the 6 months after randomisation

Relapse occurs in patients with cryptococcal disease. All patients will be receiving either treatment doses of antifungal therapy or secondary prophylaxis doses during the 6-month period of follow-up. Although all patients will be encouraged to return to the study hospital in the event of illness during the 6-month follow-up period, it is possible that, because of their location, some patients will undergo treatment elsewhere where diagnostic facilities may be less developed. This episode may only be identified at the 6-month follow-up period. For this reason, a pragmatic definition of relapse will be used. This is defined as either intensification of antifungal therapy above that according to the study antifungal schedule, or readmission for treatment of cryptococcal disease. The main outcome measure will be the cause-specific hazard of relapse, taking into account the competing risk of death.

#### Health economics

If effective, the low cost of dexamethasone makes it promising as a cost-effective intervention in low-income settings. To assess this formally, a cost-effectiveness analysis will be conducted in collaboration with the Health Economics Research Centre, University of Oxford. The objective of the analysis will be to estimate the incremental cost-effectiveness ratio (ICER), expressed as cost per life year gained and cost per Quality Adjusted Life Year (QALY) gained and per Disability Adjusted Life Year (DALY) averted of dexamethasone treatment compared with standard antifungal therapy for cryptococcal meningitis (CM).

The analysis will collect information during the study on resources used and direct and indirect costs, including health care costs (treatments, medications, consultations, initial and subsequent hospitalisations), and patient/family incurred costs (out-of-pocket costs, employment). Health-care resources used will be obtained primarily from trial case record forms. Unit costs will be obtained in each country from participating centres and national sources. Information on patient-employment status and costs will be obtained from patients by a small number of questions administered at recruitment and again at the final follow-up (10-week) visit. The main measures of effectiveness will be (a) life years gained (b) quality-adjusted life years gained (QALYs), estimated by using the EQ-5D instrument in official English, Vietnamese, and Thai languages in its three-level version, and (c) disability-adjusted life years (DALYs) averted, which measures both years of life lost because of premature mortality and years lived with disability. Life years gained will be based on the primary outcome measure of survival at 10 weeks, extrapolated by using best estimates of longer-term survival in each country for HIV-infected adults. QALY and DALY estimates will adjust the life-year estimates by taking into account secondary end points, including blindness, deafness, and other neurologic disabilities that are important sequelae of cryptococcal disease. QALY adjustment will be done by using EQ-5D-3 L responses, and DALY adjustment by using clinical judgment to align recorded morbidity with DALY states. The use of both approaches will provide internal validity checks and maximise opportunities to present relevant information to decision makers.

As unit costs, absolute risks, life expectancy, and other variables are likely to differ substantially across regions, separate cost-effectiveness estimates will be produced for Asia and Africa; however, a trial-wide estimate of effectiveness will be applied unless clear evidence exists of heterogeneity in effect across regions. All estimates of costs, outcomes, and cost-effectiveness will be reported with full recognition of uncertainty, including cost-effectiveness acceptability curve and sensitivity analyses around key parameters, including unit costs, long-term life expectancy, and disability adjustment.

The economic evaluation is concerned primarily with estimation of cost and outcome differences and cost-effectiveness rather than hypothesis testing, and a power calculation for a ratio statistic is likely to be highly uncertain, especially as the DALY/QALY measure (the denominator) will itself be a composite of survival and quality/disability adjustment. The proposed size of the study (880 patients) should permit cost differences of 12% or greater to be reliably detected by assuming a coefficient of variance of 60%.

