### Secondary end points

#### Survival until 6 months after randomisation

Relapse occurs in cryptococcal meningitis. Most cases occur within 6 months of diagnosis. We will collect survival data at 6 months (alive versus date of death) to ensure that any survival benefit at 10 weeks is sustained at 6 months, and not negated by, for example, a higher relapse rate in patients receiving steroids.

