### Analysis

#### Analysis of the primary end point and 6-month mortality

The analysis will be based on a stratified Cox proportional hazards model allowing for separate baseline hazards for each continent (Asia or Africa) and treatment allocation as the only covariate. The stratification is based upon the expectation of different mortalities in the control arm by continent but similar (relative) effects of the intervention across continents. The proposed test is essentially equivalent to using a stratified log‒rank test to compare the two treatment arms. We prefer to use the Cox model as it automatically provides treatment effect estimates and confidence intervals in addition to the *P* value.

In a second stage, overall survival will be modelled by using the Cox proportional hazards regression model with stratification by continent and the following covariates (in addition to the treatment group): country, baseline fungal load, Glasgow coma score less than 15, and ARV status at study entry (ARV naïve or experienced).

Potential heterogeneity of the treatment effect will be assessed based on appropriate interaction (likelihood ratio) tests and the following predefined subgrouping variables:

ContinentCountryIDSA indications for steroid treatment at baseline (cryptococcoma with mass effect, acute respiratory distress syndrome or IRIS: yes or no)Glasgow coma score <15 (yes or no)Naïve to ARVs at study entry versus on ARVS at study entry

All Cox regressions and sub-group analyses will be performed for the primary end point (10-week survival) as well as for 6-month survival. Kaplan-Meier plots and explicit survival estimates at 10 weeks and 6 months of follow-up will also be calculated for the full populations and for each continent separately.

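### The economic base case extrapolates life years from the 10-week survival difference although the trial observes survival and disability by arm to 6 months

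*Protocol article*

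**What the plan says.** In the Protocol article, Health economics, the basis of the effectiveness measure is explicit: "Life years gained will be based on the primary outcome measure of survival at 10 weeks, extrapolated by using best estimates of longer-term survival". The external source is "best estimates of longer-term survival in each country for HIV-infected adults". QALY and DALY estimates are described as adjustments of these life years, so all three cost-effectiveness ratios rest on the same survival basis. The same section reports uncertainty by acceptability curve and by sensitivity analyses. It names unit costs, long-term life expectancy and disability adjustment as examples.

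Elsewhere the article gives 6-month data a specific purpose. Under Survival until 6 months after randomisation, survival is collected "to ensure that any survival benefit at 10 weeks is sustained at 6 months, and not negated by, for example, a higher relapse rate". Clinical monitoring adds: "Disability and mortality at 6 months and evidence of morbidity (including IRIS) since last seen (week 10) will be collected". Under Analysis of the primary end point and 6-month mortality: "All Cox regressions and sub-group analyses will be performed for the primary end point (10-week survival) as well as for 6-month survival". Kaplan-Meier survival estimates at 6 months are also planned.

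**The concern.** The economic analysis stops using randomised survival data at week 10 and replaces the next 16 weeks with an external assumption. That is the window in which the protocol itself says an early benefit might be undone, for instance by relapse. It also opens when the antifungal schedule steps down to secondary prophylaxis. If country-level survival is applied alike to 10-week survivors of both arms, which is the natural reading, the arms cannot converge or diverge after week 10 in the base case, even if the trial shows that they did.

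At stake is the denominator of the cost per life year, QALY and DALY. For a given incremental cost, a twofold overstatement of life years gained halves the reported cost per life year.

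**Working it through.** **Inputs from the protocol** (Sample size and power considerations): hazard ratio 0.7; 10-week control mortality 30% or 50%, falling to 22% or 38%. Survival is observed to 6 months, so the window is 26 − 10 = 16 weeks, or 16/52 = 0.308 years.

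**Assumptions, not in the documents:** remaining life expectancy from week 10, L = 5, 10 or 20 years, undiscounted and the same for survivors of both arms. The share of the week-10 difference present at 6 months is r. It is measured against what equal mortality in both arms would leave, because that common mortality is already inside L. The difference is taken to change linearly over the 16 weeks.

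**Step 1: reproduce the protocol's effect.** Treated risk = 1 − (1 − p)^0.7.
- p = 0.30: 1 − 0.70^0.7 = 0.221, so d = 0.079 (protocol: 22%).
- p = 0.50: 1 − 0.50^0.7 = 0.384, so d = 0.116 (protocol: 38%).

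Both agree with the stated figures.

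**Step 2: life years gained per patient.**
- Plan as written: d × L.
- With 6-month survival: d × (1 + r)/2 × 0.308 + r × d × (L − 0.308).

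At r = 1 the two are equal. The ratio of plan to 6-month version does not depend on d.

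**Step 3: results for d = 0.079.**

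| L (years) | Plan | r = 1 | r = 0.5 | r = 0 | r = 1.5 |
|---|---|---|---|---|---|
| 5 | 0.40 | 0.40 | 0.20 | 0.012 | 0.59 |
| 10 | 0.79 | 0.79 | 0.40 | 0.012 | 1.18 |
| 20 | 1.58 | 1.58 | 0.80 | 0.012 | 2.37 |

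Worked example, L = 10 and r = 0.5: 0.0791 × 0.75 × 0.308 + 0.5 × 0.0791 × 9.692 = 0.018 + 0.383 = 0.40. The plan gives 0.79, a ratio of 1.97. For L = 5 and 20 the ratios are 1.94 and 1.98.

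At r = 0 the plan still credits 0.40 to 1.58 years against about 0.012. At r = 1.5 it credits about two thirds of the gain (0.79/1.18 = 0.67). For p = 0.50 the plan credits 0.58, 1.16 and 2.31 years, against about 0.018 at r = 0.

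**Step 4: does the planned sensitivity analysis cover this?** The plan's quantity is d × L with d fixed at week 10. Varying life expectancy moves L and so rescales the result. It does not change d and cannot represent convergence of the arms.

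**The case against.** The case for leaving the plan alone has several parts.

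- **The size is hypothetical.** This stands. No 6-month mortality or life expectancy is given, nothing shows that the arms will converge, and a benefit that grew would be under-credited.
- **The article does not say that both arms get identical curves, or that 6-month data may not inform the external estimates.** True, but the named source is country-level survival of HIV-infected adults, and no sentence brings 6-month survival by arm into the life years.
- **Uncertainty is covered.** The list of sensitivity analyses is open-ended, and 6-month Cox and Kaplan-Meier results would appear beside the economic result, so a lost benefit would be visible. That helps the reader but leaves the base case as stated.
- **This is a secondary analysis.** True. The primary end point and sample size are untouched.

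Two stronger readings are tempting and are not supported.

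- **Missed relapse costs.** A reader might infer from "again at the final follow-up (10-week) visit" that readmission and retreatment costs after week 10 are lost. That phrase governs only the questions on patient employment and costs. Health-care resource use comes mainly from case record forms, includes later hospital admissions, and has no stated week-10 cut-off.
- **Overstatement from ordinary later deaths.** A reader might argue that if 10% of week-10 survivors die by month 6 in each arm, the gain shrinks from 0.08 to 0.78 × 0.90 − 0.70 × 0.90 = 0.072, so the plan overstates. But remaining survival from week 10 already includes such deaths: 0.08 × L from week 10 equals 0.08 × the mean time lived in the 16 weeks plus 0.072 × L from month 6. An overstatement arises only if the external estimate omits deaths in that window.

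**Conclusion.** The point holds as a weakness in a stated analysis choice. The base case fixes life years on the week-10 difference and ignores the randomised data collected to test whether that difference lasts. If mortality after week 10 is the same in both arms and the external estimate captures it, there is no error. If half the gap remains, life years gained are overstated about 1.9 to 2.0 times for L between 5 and 20 years. If the gap closes, the plan still credits about 0.08 × L per patient at 30% control mortality, about 0.4 to 1.6 years. If the gap grows, the error reverses. These figures rest on the assumed L and r, on no discounting, on linear change over the 16 weeks, and on the same external survival being applied to both arms. The point concerns the cost-effectiveness ratios only. It should be corrected, because the better method uses data already planned.

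**What to change.** State that life years, QALYs and DALYs in the base case use observed survival and disability by arm to 6 months, and that extrapolation starts at 6 months. Mean survival time to 6 months can be read from the Kaplan-Meier curves already planned. Show the 10-week version as a sensitivity analysis.

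The cost is a change of analysis wording and slightly more work. Survival and disability to 6 months are already collected. The one real difficulty is utilities: the article does not state that EQ-5D is collected at 6 months, and that contact may be by telephone. Utilities after week 10 may therefore have to be carried forward or mapped from 6-month disability, and the method chosen should be stated in advance.
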